## Reporting of serious adverse events

Information on all serious adverse events is registered in the SAE form included in Trial Master File. All serious adverse events is reported to principle investigator ([name]) or Sponsor ([name]) no later than first coming workday after investigator has become aware of the event. The immediate report will be followed by a detailed written report within 24 hours. Adverse reactions, that are not life threatening and mild in character, do not require medical attention or intervention and are insignificant to the patients’ further involvement in this trial will not be reported to sponsor. These will be registered in case report forms and available to monitoring units and sponsor at any time.

## Reporting of Suspected Unexpected Serious Adverse reactions (SUSAR’s)

Any serious adverse event that is assessed to have causal relation to the trial drug is a serious reaction. Unexpected serious reactions (not previously described in relevant product information(32)) are registered as SUSAR’s.

Sponsor will gather all relevant information about the SUSAR’s. In case of death or life threatening reactions The Danish Health and Medicines Agency will be informed within 7 days of sponsor’s knowledge of the reaction.

Within 8 days a report of sponsor and investigators follow-up on the incident will be forwarded. Reporting will be done electronically.

All other SUSAR’s will reported to The Danish Health and Medicines Agency within 15 workdays.

In case of a SUSAR sponsor and principle investigator will assess the consequences and impact of the event before unblinding. Hereafter unblinding will be performed before reporting to authorities. In the evaluation of possible SUSAR’s investigators brochure for Xifaxan 550 mg (provided by Norgine Denmark, see appendix) will be addressed.

# Statistics

Statistics are based on an assessment of demography and incidence of liver cirrhosis Child-Pugh B and C in the capital region of Denmark, which will be the inclusion area of patients.

Taking exclusion criteria in to consideration, we have estimated that a realistic inclusion figure will be between 60 and 70 patients. In this group of patients we expect a drop out rate of 20-25 %.

We expect to achieve a reduction in HVPG as well as an increase in glomerular filtration rate (GFR). The smallest clinically relevant difference in measurements are set to 20 %; that is, a 20% reduction in HVPG and a 20% increase in GFR.

Data will be analyzed paired and independently (as changes between individuals and difference between groups).

Parametric and non-parametric analysis will be used, depending on the underlying distribution.

The following power calculation is based on Student t-test, with a paired testing, and a fixed sample size of 32 treated patients.

Evident information on mean values of GFR and HVPG is inconclusive. The following analyses are made on available sources(39;40) and our best estimate.

In consideration of the relatively small population size, we plan no interim analyses.

Therefore, including a dropout rate of minimum 20-25 %, our aim is to include 32 + 6 = 38 patients for treatment and 16 + 3 = 19 patients for placebo. Hence, the following power calculations are done with a fixed sample size of 48 patients, 32 in treatment group, 16 in placebo group.

The trial will be disrupted when we have included enough patients to meet sample size and power.

We plan to perform both intention to treat and pr. Protocol analyses. Hence, all patient data available will be incorporated into analyses.

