# Randomisation methods

The study is conducted as a randomised placebo controlled clinical trial, randomised in the ratio 2:1, rifaximin and placebo, respectively.

We expect no changes in clinical state, haemodynamics or other parameters in the patients receiving placebo, therefore we find it adequate to randomize in the ratio 2:1.

The study is dimensioned at including 32 patients in the rifaximin group and 16 patients in the placebo group.

The trial is a multi centre study, with seven hospital departments screening possible candidates for participation and referral to primary centre of investigation.

Packing and labelling will take place at the regional hospital pharmacy. Labelling will be performed after applicable legislation including name of pharmacy, trial name, patient name, CPR and trial number, dose, storage and contact information of principle investigator.

The randomization list in the ratio 2:1 will be produced electronically. This randomization list will be stored at the regional pharmacy. Only personnel at the pharmacy will know the randomisation code.

Participants will be assigned to a randomisation number electronically.

This two-digit trial number will henceforth identify trial participants.

The sponsor, principle investigator and sub investigators, nurses, laboratory assistants or personnel involved in the care for the trial participant will have no knowledge of the blinding. Coded envelopes with randomisation keys to each participant will be kept at Hvidovre Hospital in a safe and locked drawer. These envelopes will be available to sponsor and investigators at all times in case unblinding should be necessary.

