### Paired analysis:

We expect a 20 % reduction in HVPG.

Mean HVPG in patients with liver cirrhosis: 17,9 mmHg(39)

DIFF: (17,9 x 0,2) ~3,58 mmHg

Probability of falsely rejecting the null-hypothesis (type 1 error): 0,05 (95% CI)

Standard Deviation equal to 95% of readings: 3,9 mmHg

The paired comparison including 32 rifaximin treated patients will have a power of **0,998** expecting a 20 % (3,1 mmHG) reduction in HVPG.

We expect a 20 % increase in GFR.

Mean GFR in patients with liver cirrhosis and non-refractory ascites: 69 mL/minute(40)

DIFF: (69x 0,2) ~13,8 ml/minute

Probability of falsely rejecting the null-hypothesis (type 1 error): 0,05 (95% CI)

Standard Deviation equal to 95% of readings: 16 ml/minute

The paired comparison including 32 rifaximin treated patients will have a power of **0,996** expecting a 20 % reduction in GFR.

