### Independent analysis:

We expect a 20 % reduction in HVPG. Same values as for paired analysis are applied.

Relation between treated and controls: 2:1

We have 32 experimental patients and 16 patients receiving placebo. The HVPG within the subject group was normally distributed with standard deviation 3,9 mmHg. If the true difference in the experimental and control means is 3,1 mmHg, we will be able to reject the null hypothesis that the population means of the experimental and control groups are equal with probability (power) **0,835**.

We expect a 20 % increase in GFR. Same values as for paired analysis are applied.

Relation between treated and controls: 2:1

We have 32 experimental patients and 16 patients receiving placebo. The GFR within the subject group was normally distributed with standard deviation 16 ml/minute. If the true difference in the experimental and control means is 13,8 ml/minute, we will be able to reject the null hypothesis that the population means of the experimental and control groups are equal with probability (power) **0,79**.

We do not expect any changes in patients receiving placebo on any of the outcome measures.

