## Patient disadvantages and risks

Participants randomised to rifaximin treatment may experience side effects to medication; Risks and side effects related to medication and placebo are elaborated on p. 18.

All investigations are thoroughly described in appendix 6. Risks and complications related to investigations are elaborated on pp. 14-16.

Participation in this trial requires more than two days extra hospitalisation and an extra outpatient visit, during the 4 weeks of trial course. Moreover, we repeat a whole series of investigations, not all relevant or beneficial for the individual patient at the time of investigation. There are some nuisances and pain related to the investigations, even though we will try to compensate and relieve the participants as much as possible. The patients will, irrespective of their participation in this trial be offered elucidation of their liver cirrhosis with liver vein catheterisation, and we have placed the initial investigations in relation to this admission to hospital, hence to minimize days of hospitalisation.

One third of participants will receive placebo medicine. At present, there is no registered medication, that prevents bacterial translocation from the gut and actively lowers the hepatic venous pressure, and it lacks yet to be proven whether rifaximin has an effect on these parameters. Hence, patients are not withheld proved active medication. All patients continue their regular prescribed medication during the trial period.

Participants randomised to placebo treatment will most likely not experience any differences or improvement in symptoms and events related to their disease.

The use of placebo is considered necessary to secure that observed effects are ascribed to rifaximin with certainty.

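### The one-arm before-after test and the randomised rifaximin-placebo comparison stand unranked, so an effect could be claimed without using the placebo data

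*Protocol*

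**What the plan says.** The Statistics section plans two kinds of analysis: "Data will be analyzed paired and independently (as changes between individuals and difference between groups"). It then names the basis of the power calculation: "The following power calculation is based on Student t-test, with a paired testing, and a fixed sample size of 32 treated patients". Later in the same section it says that "the following power calculations are done with a fixed sample size of 48 patients, 32 in treatment group, 16 in placebo group".

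Under Power calculation, the paired analysis gives power 0.998 for HVPG and 0.996 for GFR in 32 rifaximin patients. The independent analysis gives 0.835 and 0.79 for 32 rifaximin against 16 placebo patients. On the SD and the difference, the independent analysis says only "Same values as for paired analysis are applied".

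The Data management section says that the primary outcomes are analysed first, but not by which test. Randomisation methods and the independent analysis both assume no change on placebo. The section on patient disadvantages and risks gives the reason for the control arm: "The use of placebo is considered necessary to secure that observed effects are ascribed to rifaximin with certainty".

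**The concern.** A paired test in the rifaximin arm asks whether rifaximin patients changed between day 1 and day 29-32. It does not ask whether they changed more than placebo patients. Anything that moves both arms over four weeks enters the paired result as if it were a drug effect: re-admission, drinking habits, other medication, or regression after selecting patients with an HVPG of at least 10 mmHg.

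The paired test is evidence about the drug only if placebo patients do not change. The protocol assumes this, but the placebo arm is there to check it. With the two tests unranked, a significant paired result beside a non-significant randomised comparison could be reported as success on a primary outcome. The printed powers of 0.998 and 0.996 also suggest a far stronger trial than the randomised comparison provides.

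**Working it through.** **Inputs from the protocol (Power calculation).** Mean HVPG 17.9 mmHg, 20% difference 3.58 mmHg, SD 3.9. The HVPG power sentences print 3.1 mmHg. Mean GFR 69 ml/min, 20% difference 13.8, SD 16. Arms 32 and 16. Alpha 0.05; sidedness is not stated, and two-sided is used here.

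**Step 1: reproduce the paired power.** Noncentral t, df 31, noncentrality = difference/SD × √32.
- HVPG, 3.58: 3.58/3.9 × 5.657 = 5.19, power 0.999 (printed 0.998). With 3.1 it is 0.992.
- GFR: 13.8/16 × 5.657 = 4.88, power 0.997 (printed 0.996).

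**Step 2: reproduce the between-arm power.** df 46, noncentrality = difference/(SD × √(1/32 + 1/16)), with √(1/32 + 1/16) = 0.306.
- HVPG, 3.58: 3.58/(3.9 × 0.306) = 3.00, power 0.835, as printed.
- HVPG, 3.1: 3.1/(3.9 × 0.306) = 2.60, power 0.72.
- GFR: 13.8/(16 × 0.306) = 2.82, power 0.787 (printed 0.79).

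So 0.835 was obtained with 3.58, not with the 3.1 printed beside it. One-sided testing with 3.1 gives 0.819, but one-sided GFR power would be 0.871, so a one-sided test does not explain both outcomes.

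**Step 3: the paired test when the drug does nothing.** Assume both arms shift equally. The 5% and 10% are illustrative and are not in the protocol. The SDs are used as the protocol's paired calculation uses them.

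| Outcome | Common shift | Noncentrality (n = 32) | Probability that the paired test is significant |
|---|---|---|---|
| HVPG | 5% = 0.895 mmHg | 0.895/3.9 × 5.657 = 1.30 | 0.24 |
| HVPG | 10% = 1.79 mmHg | 2.60 | 0.71 |
| GFR | 5% = 3.45 ml/min | 3.45/16 × 5.657 = 1.22 | 0.22 |
| GFR | 10% = 6.9 ml/min | 2.44 | 0.66 |

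The between-arm test stays at 0.05 in all four rows, because a common shift cancels.

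**Step 4: would separate tests in each arm protect?** At the 10% shift, the same paired test in 16 placebo patients (√16 = 4, df 15) has noncentrality 1.79/3.9 × 4 = 1.84 for HVPG and 6.9/16 × 4 = 1.73 for GFR. It is significant with probability 0.405 and 0.365. Significance on rifaximin but not on placebo then occurs with probability 0.711 × (1 − 0.405) = 0.42 for HVPG and 0.657 × (1 − 0.365) = 0.42 for GFR, with no drug effect. The 2:1 allocation makes this pattern likely.

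**Step 5: power of the proposed test.** ANCOVA at 32 + 16, df 45. The correlation r between baseline and final value is not in the protocol and is assumed. The residual SD depends on what 3.9 and 16 are:
- SDs of a single reading: residual SD = SD × √(1 − r²).
- SDs of change: residual SD = SD × √((1 + r)/2).

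| Reading of the SD | Outcome | r = 0.3 | r = 0.5 | r = 0.7 |
|---|---|---|---|---|
| Single reading | HVPG, 3.58 | 0.87 | 0.92 | 0.98 |
| Single reading | GFR, 13.8 | 0.82 | 0.89 | 0.97 |
| Change | HVPG, 3.58 | 0.95 | 0.92 | 0.89 |
| Change | GFR, 13.8 | 0.93 | 0.89 | 0.85 |

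Every entry exceeds the unadjusted 0.835 or 0.79, but the size of the gain, and its trend with r, depend on which SD is meant.

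**The case against.** The strongest reply is that the protocol does power the randomised comparison. It fixes 48 patients, 32 and 16, and prints 0.835 and 0.79 for them. The arithmetic supports this: 80% power needs only 12 (HVPG, 3.58 mmHg) or 13 (GFR) rifaximin patients for the paired test, but 15 or 17 placebo patients for the between-arm test at 2:1. A reader might infer from the sentence on paired testing that the trial was sized on a before-after test; the sample size itself does not support that. This part of the reply stands. It does not supply the missing ranking.

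Three other readings are tempting and not supported:
- **That leaving out ANCOVA is an error that wastes power.** A covariate model may properly sit in a statistical analysis plan that is not shown, and the gain rests on an assumed correlation. ANCOVA is the recommended remedy here, not the fault.
- **That one SD for both tests is wrong unless r = 0.5.** This follows only if the between-arm test compares final values. If it compares changes, one SD of change serves both tests at any r. The protocol does not say which is meant, so clarification is needed.
- **That choosing a parametric or non-parametric test by the observed distribution is a defect.** That detail can be left to the analysis plan and is not part of this point.

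It can also be said that the trial calls itself mainly explorative, and that its reason for placebo shows attribution was meant to rest on the control arm. But the protocol names two primary outcomes and powers both with formal tests. Its reason for placebo supports the ranking asked for here.

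**Conclusion.** The point holds in this form: the protocol gives a one-arm before-after test equal standing with the randomised comparison, calls the former the basis of its power calculation, and never says which decides. A claim of effect without placebo support is therefore within the plan, against the protocol's own reason for having placebo.

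The size is illustrative. The rates in Step 3 assume equal shifts in both arms, no drug effect, two-sided 0.05, and 3.9 and 16 as SDs of change. The protocol expects no placebo change; if that were exactly true, the paired test would keep its nominal 5%. The mechanism does not depend on the particular shifts.

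Two smaller points follow from the same text. The HVPG between-arm power is 0.835 for 3.58 mmHg and 0.72 for the printed 3.1. The kind of SD is not stated.

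**What to change.** 1. Name one primary test for each of HVPG and GFR: the rifaximin-minus-placebo difference at day 29-32, by ANCOVA with the baseline value as covariate.
2. Label the within-arm paired tests descriptive, with no claim of effect to rest on them.
3. Quote only the between-arm power as the power of the trial; remove 0.998 and 0.996 from that role and amend the sentence that bases the calculation on paired testing.
4. State whether 3.9 and 16 are SDs of a single reading or of change.
5. Reconcile 3.1 mmHg with 3.58 mmHg, and print the power that belongs to the figure kept.

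The cost is wording and one degree of freedom for the covariate. Both baselines are already measured on day 1, so no new data, visits or patients are needed for the change of primary test. If 3.1 mmHg is the figure intended, the unadjusted HVPG power must be reported as 0.72.

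### The dropout allowance of 6 and 3 covers 15.8% loss, not the stated 20-25%, so enrolling 38 + 19 does not in expectation deliver the two between-group powers

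*Protocol*

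**What the plan says.** The Statistics section judges 60 to 70 inclusions realistic and adds: "In this group of patients we expect a drop out rate of 20-25" per cent. It then sets the target, "including a dropout rate of minimum 20-25" per cent: "our aim is to include 32 + 6 = 38 patients for treatment and 16 + 3 = 19 patients for placebo". The next sentence says that "the following power calculations are done with a fixed sample size of 48 patients, 32 in treatment group, 16 in placebo group". On ending recruitment the section says: "The trial will be disrupted when we have included enough patients to meet sample size and power".

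The Randomisation methods section puts the size differently: "The study is dimensioned at including 32 patients in the rifaximin group and 16 patients in the placebo group". The paired power calculation uses the 32 treated patients. The independent calculation uses 32 against 16 and states power 0.835 for HVPG and 0.79 for GFR. The Finance and funding section sizes the drug supply for 38 and 19 patients.

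**The concern.** The allowance looks as if it was added as a share of the completers (6/32 = 3/16 = 18.75%). A dropout rate applies to those enrolled, so the completers should be divided by one minus the rate. If so, the target contradicts the rate it claims to include, and the evaluable sample is expected to fall short of 32 + 16.

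HVPG and GFR are the two primary outcomes, and the comparison with placebo is the randomised one. A reader would take 0.835 and 0.79 as the powers that an enrolment of 38 + 19 provides. Two wordings add to the doubt. Both 32 + 16 and 38 + 19 are described as numbers to include, and the sentence on ending recruitment does not say whether it counts patients enrolled or patients completing.

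**Working it through.** **Inputs (Protocol).** Completers 32 + 16; enrolment 38 + 19; dropout 20-25% (Statistics). HVPG SD 3.9 mmHg; difference 3.58 mmHg as derived (17.9 × 0.2), but 3.1 mmHg as written with the stated power. GFR SD 16 ml/min, difference 13.8 ml/min. Type I error 0.05 (Power calculation). Sidedness is not stated; two-sided is assumed because it reproduces the stated powers.

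**1. Loss that the allowance covers.** 6/38 = 3/19 = 9/57 = 15.8%.

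**2. Enrolment that would match.** N/(1 − d):
- d = 0.20: 32/0.80 = 40 and 16/0.80 = 20, total 60.
- d = 0.25: 32/0.75 = 42.7, so 43; 16/0.75 = 21.3, so 22; total 65.

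The stated 38 + 19 matches only N × (1 + d) at 20%, rounded down (38.4 and 19.2). Even that formula gives 40 + 20 at 25%.

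**3. Completers expected from 38 + 19.**
- 20%: 38 × 0.80 = 30.4 and 19 × 0.80 = 15.2.
- 25%: 38 × 0.75 = 28.5 and 19 × 0.75 = 14.25.

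In whole patients this is about 30 + 15 and 28 + 14.

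**4. Chance of keeping both arms at size.** Binomial tails, same rate in both arms, patients independent:
- 20%: P(at least 32 of 38) = 0.340; P(at least 16 of 19) = 0.455; product 0.155.
- 25%: 0.128 × 0.263 = 0.034.

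**5. Between-group power.** Noncentral t with n1 + n2 − 2 degrees of freedom and noncentrality δ / (σ √(1/n1 + 1/n2)). For 32 + 16 the root is √0.09375 = 0.306. This gives 3.58/(3.9 × 0.306) = 3.00 for HVPG and 13.8/(16 × 0.306) = 2.82 for GFR.

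| Completers | HVPG, 3.58 mmHg | HVPG, 3.1 mmHg | GFR, 13.8 ml/min |
|---|---|---|---|
| Stated, 32 + 16 | 0.835 | (0.835 is printed beside 3.1) | 0.79 |
| 32 + 16 | 0.835 | 0.720 | 0.788 |
| 30 + 15 | 0.810 | 0.690 | 0.760 |
| 28 + 14 | 0.781 | 0.659 | 0.730 |

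The stated GFR power reproduces. The stated HVPG power reproduces with 3.58 mmHg and not with the 3.1 mmHg printed with it.

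**6. Paired power.** Noncentral t with n − 1 degrees of freedom and noncentrality (δ/σ)√n, treated patients only. Stated: HVPG 0.998, GFR 0.996.

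| Treated completers | HVPG, 3.58 | HVPG, 3.1 | GFR |
|---|---|---|---|
| 32 | 0.999 | 0.992 | 0.997 |
| 30 | 0.998 | 0.988 | 0.995 |
| 28 | 0.997 | 0.982 | 0.993 |

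**The case against.** The best case for the plan is that the slip is small beside the uncertainty of its inputs. At 20% dropout the enrolment gap is two patients in one arm and one in the other, and the cost is about 2.5 to 3 points of power. The protocol calls its aim mainly exploratory and admits that its means are best estimates from inconclusive sources. The 3.58 against 3.1 mmHg conflict costs 0.835 − 0.720 = 11.5 points at full size, more than the dropout shortfall. All of this stands, and it limits the weight of the point.

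Some stronger readings are tempting but not supported:
- A reader might infer that none of the stated powers is delivered. The paired powers use no placebo patients and stay close to their stated values.
- A reader might infer that 32 + 16 cannot be reached. The shortfall is in expectation; by chance both arms could still be kept at size.
- A reader might take the 32 + 16 under Randomisation methods as a rival enrolment target. It can equally be read as the evaluable number that the power section uses. The wording is loose, not plainly contradictory.
- A reader might say that the recruitment stop names no number at all. It refers to sample size as well as power, and 48 is stated just before it. It could mean recruiting until 48 are evaluable. But it speaks of inclusion and not completion, and the aim and the drug supply are both fixed at 38 + 19, so it does not rescue the target.

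The intention-to-treat analysis does not clearly rescue it either. A change in HVPG or GFR needs the repeat measurement on days 29-32, no follow-up of dropouts is planned, and missing values are left empty. A patient classed as a dropout only because of the tablet count might still have that measurement, but the protocol gives no figure for this.

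**Conclusion.** The point holds. The enrolment target claims to absorb at least 20-25% dropout and absorbs 15.8%. At the plan's own rate, the two between-group powers are not delivered in expectation. GFR power is about 0.76 to 0.73, not 0.79. HVPG power is about 0.81 to 0.78, not 0.835, if the difference is 3.58 mmHg. If 3.1 mmHg is meant, the figure is 0.69 to 0.66, and most of that gap is not due to dropout. The between-group loss from dropout alone is about 2.5 to 3 points at 20% and 5 to 6 points at 25%. The paired results do not change in any way that matters.

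This rests on a two-sided 0.05 test, equal dropout in the two arms, the plan's standard deviations, and the 20-25% meaning patients without a usable second measurement. Severity is minor to moderate.

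**What to change.** 1. Reconcile the HVPG difference (3.58 or 3.1 mmHg) first, because the HVPG power cannot be restated until that is settled.
2. Then do one of two things. Either restate the between-group powers at the expected completers, 30 + 15 to 28 + 14 (GFR 0.76 to 0.73; HVPG 0.81 to 0.78 with 3.58 mmHg, or 0.69 to 0.66 with 3.1 mmHg). Or state that 38 + 19 allows for only about 16% dropout and give the reason for that lower rate.
3. Under Randomisation methods, say that 32 + 16 is the evaluable number.
4. Replace the sentence on ending recruitment with a fixed number randomised.

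These are text changes. They cost only a less favourable power figure or a lower stated dropout rate.

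If 32 + 16 completers are required, the matching enrolment is 40 + 20 (20%) or 43 + 22 (25%). Both lie within the protocol's own 60 to 70, but this is optional. Supply is the constraint. The Handling of trial medication section gives both 34 and 36 tablets for the second container, which makes 28 + 34 = 62 or 28 + 36 = 64 per patient, and the two must be reconciled. The 2520 and 1260 tablets cover 40 + 20 at 62 each (2520/62 = 40.6; 1260/62 = 20.3) but only 39 + 19 at 64 each (39.4; 19.7). Enrolling 43 + 22 would need more in either case (43 × 62 = 2666).

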## Finance and funding

Rifaximin tablets of 550 mg and placebo tablets in the amounts 2520 tablets (180 blister of 14) and 1260 tablets (90 blisters of 14) respectively, equal to treatment of 38 patients with rifaximin and 19 patients with placebo, are delivered by Norgine Denmark free of costs. See appendix for contracts and agreements.

Norgine Denmark is not further involved in the trial and has no influence whatsoever on the design and methods, nor on compilation and publication of results. For business contract see appendix 7.

Norgine Denmark has not provided funding in addition to the above.

Sponsor and principle investigator have invented the overall template of this research project and have taken initiative to execute it. None of the involved researchers have economic interests or affiliations in private firms, funds or similar.

Research results obtained from this trial are of scientific interest entirely. There are no economic or commercial conflicts regarding the investigations.

The salary of primary investigator is partly financed through employment at Department of clinical physiology and nuclear medicine, Hvidovre Hospital and partly through scholarships and funds.

The department of gastroenterology Hvidovre Hospital will undertake expenses regarding extra outpatient visits and admission to hospital for the purpose of participating in this research project.

Additional costs and expenses will be financed through funds. Expenses regarding analyses and investigations will be covered through funds.

At present we have received grants from The medical foundation of Hvidovre Hospital for the treatment of liver diseases (122.000 kr. + 150.000 kr.) and the Research Foundation for the Capital Region of Denmark (1.000.000 kr.), The Research Foundation Hvidovre Hospital (50.000 kr.), Novo Nordisk Foundation (300.000 kr.), Aase og Ejnar Danielsens Fond (200.000 kr.) and Inge og Per Refshalls Fond (32.400 kr.).

Contributions and scholarships are placed on a research account administered by Hvidovre Hospital. Eventual surplus will be used for remuneration of the study nurse affiliated to this trial. If not relevant, scholarships will be repaid to donors.

Trial participants will be reimbursed for their transportation expenses, after State rates and will be offered remuneration for additional time consumption, Dkr 1500,- in relation to this trial.

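### The recruitment target of 38 + 19 = 57 absorbs 15.8% dropout, not the stated minimum of 20-25%, so the two between-arm powers are modestly overstated

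*Protocol*

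**What the plan says.** All the relevant statements are in the protocol.

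- **Statistics, expected loss:** "In this group of patients we expect a drop out rate of 20-25" per cent.
- **Statistics, target:** the target is introduced as "including a dropout rate of minimum 20-25" per cent, and then given as "our aim is to include 32 + 6 = 38 patients for treatment and 16 + 3 = 19 patients for placebo".
- **Statistics, basis for power:** "the following power calculations are done with a fixed sample size of 48 patients, 32 in treatment group, 16 in placebo group".
- **Independent analysis:** the between-arm powers, 0,835 for HVPG and 0,79 for GFR, rest on the same numbers: "We have 32 experimental patients and 16 patients receiving placebo".
- **Finance and funding:** the donated tablets are described as "equal to treatment of 38 patients with rifaximin and 19 patients with placebo".

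The Statistics section also puts realistic inclusion at 60 to 70 patients. It says that the trial ends once enough patients have been included to meet sample size and power.

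**The concern.** The dropout rate, the inclusion target and the evaluable number behind the power calculation are tied by simple arithmetic, and the three stated values do not fit together. This is a different matter from whether 48 or 57 is the sample size. Even if 57 is accepted as the number to include and 48 as the number to analyse, 57 is too few for a loss of 20-25%.

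What is at stake is the power of the comparison of rifaximin with placebo on the two primary outcomes. The printed between-arm powers assume 32 and 16 patients with usable data. If recruitment succeeds exactly as planned and dropout is exactly as expected, fewer will have them.

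**Working it through.** **Inputs.** Dropout 20-25%, target 38 + 19 and evaluable 32 + 16 are from Statistics. The differences and standard deviations are from Paired analysis and Independent analysis: HVPG 3.58 mmHg (20% of 17.9) with SD 3.9; GFR 13.8 ml/min (20% of 69) with SD 16. The type 1 error is 0.05. The protocol does not state sidedness; I assume two-sided, which reproduces the printed powers.

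**1. What loss does 57 absorb?**
- 6/38 = 3/19 = 9/57 = 15.8% of those included. This is the right comparison with a dropout rate.
- As a share of the evaluable number, 6/32 = 3/16 = 18.75%, which is also below 20%.

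**2. Where does 57 probably come from?**
- 32 × 1.2 = 38.4 and 16 × 1.2 = 19.2. Rounded down, these are 38 and 19.
- So 57 matches multiplication by (1 + d) at the lowest rate, where division by (1 − d) is needed. At 25% even the multiplication gives 40 + 20 = 60.

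**3. What inclusion keeps 32 + 16 evaluable?** n/(1 − d):
- 20%: 32/0.80 = 40 and 16/0.80 = 20, total 60.
- 25%: 32/0.75 = 42.7 and 16/0.75 = 21.3, rounded up to 43 + 22 = 65 (48/0.75 = 64 without rounding per arm).

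**4. What does 57 leave?**
- 20%: 57 × 0.80 = 45.6 (30.4 + 15.2), or 30 + 15 in whole patients.
- 25%: 57 × 0.75 = 42.75 (28.5 + 14.25), or 28 + 14 in whole patients.

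**5. Between-arm power.** Two-sample t-test, noncentral t, with noncentrality δ / [SD × √(1/n₁ + 1/n₂)] and n₁ + n₂ − 2 degrees of freedom.

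| Evaluable | HVPG noncentrality | HVPG power | GFR noncentrality | GFR power |
|---|---|---|---|---|
| 32 + 16 | 3.58/(3.9 × 0.3062) = 3.00 | 0.835 (printed 0,835) | 13.8/(16 × 0.3062) = 2.82 | 0.787 (printed 0,79) |
| 30 + 15 | 3.58/(3.9 × 0.3162) = 2.90 | 0.810 | 13.8/(16 × 0.3162) = 2.73 | 0.760 |
| 28 + 14 | 3.58/(3.9 × 0.3273) = 2.80 | 0.781 | 13.8/(16 × 0.3273) = 2.63 | 0.730 |

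The first row reproduces the plan's own figures. With the fractional numbers from step 4, the powers are 0.815 and 0.766 at 20%, and 0.789 and 0.737 at 25%.

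**6. Paired power in the rifaximin arm.** At 28 to 30 patients it is 0.997-0.998 for HVPG (at 3.58 mmHg) and 0.993-0.995 for GFR, against the printed 0,998 and 0,996.

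**The case against.** The strongest reply is that little hangs on this. At 20% dropout the shortfall is about two rifaximin patients and one placebo patient, and power falls by two to three points. No endpoint, test or decision rule changes, and the Outcome measures section calls the trial mainly explorative. That stands, and it limits the severity.

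A second reply is that 57 need not be a ceiling. The sentence on ending the trial once sample size and power are met could mean recruiting until 32 + 16 are evaluable, and 60 to 70 inclusions are thought feasible. The wording is open. However, that sentence counts patients included, and both the stated target and the described drug supply are 38 + 19. The power loss is therefore conditional on recruitment stopping at 57. The mismatch between 57 and 20-25% is not.

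A third reply is that intention to treat keeps dropouts in the analysis. Some participants classed as dropouts by tablet count may still have their final measurements, so the loss could be smaller in that analysis. But under Missing data, absent values stay empty and invasive procedures are not repeated. A participant without the final catheterisation therefore has no HVPG change.

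A reader might also infer three stronger points that the protocol does not support:

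- **All four printed powers are overstated.** The two paired powers use only the rifaximin arm and stay above 0.99 (HVPG at 3.58 mmHg).
- **Withdrawals for antibiotics, encephalopathy or unblinding come on top of the 20-25%.** The Dropout section defines dropout by tablets taken or withdrawn consent, but the Statistics section does not say whether its rate uses that definition or covers every loss. This needs clarifying; it is not a demonstrated extra loss.
- **The drug supply rules out 60 patients.** It is described as covering 38 + 19, but by tablet count the answer depends on the packs. Handling of trial medication gives both 34 and 36 tablets for the second container, so 62 or 64 per participant with the first 28. At 62, 2520/62 = 40.6 and 1260/62 = 20.3, enough for 40 + 20. At 64, 2520/64 = 39.4 and 1260/64 = 19.7, not enough. Those two pack figures must be reconciled first.

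**Conclusion.** The point holds, at moderate severity. The stated target is not consistent with the stated dropout rate at either end of its range: 57 absorbs 15.8%, while 20-25% requires 60 to 65. If recruitment stops at 57 and dropouts lack a final measurement, the between-arm power falls by about 2 to 5 points for HVPG and 2 to 6 for GFR. At 25% dropout, HVPG goes below 0.80, and GFR, already just under 0.80, goes further below.

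These figures take the plan's differences and standard deviations as given. HVPG is calculated at 3.58 mmHg because only that difference reproduces 0,835. The 3,1 mmHg printed beside that power is a separate inconsistency, and gives about 0.72 at 32 + 16. It has a larger effect than the dropout error and should not be confused with it.

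**What to change.** In the Statistics section, do one of the following:

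- State that 38 + 19 allows for about 16% loss, and drop the claim that it includes 20-25%.
- Keep 20-25%, state that 57 included are expected to leave about 30 + 15 to 28 + 14 evaluable, and restate the between-arm powers as about 0.81-0.78 for HVPG (at 3.58 mmHg) and 0.76-0.73 for GFR.

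In either case, add one sentence saying whether recruitment stops at 57 included or at 32 + 16 evaluable, and one saying whether the dropout rate counts participants removed under Withdrawal of trial participants.

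The cost is a few sentences and, under the second option, two slightly less favourable powers. No extra patients are needed. If the sponsor prefers to secure 32 + 16 evaluable, the target becomes 60 to 65. That lies within the protocol's own feasible range, but the supply would have to be checked. The upper end exceeds it on either pack size: 43 × 62 = 2666 against 2520 rifaximin tablets, and 22 × 62 = 1364 against 1260 placebo tablets.
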